## Abstract

**Background:**

The aim of the present research is to conduct a fully powered explanatory trial to evaluate the efficacy of a brief self-regulation intervention to increase walking. The intervention will be delivered in primary care by practice nurses (PNs) and Healthcare Assistants (HCAs) to patients for whom increasing physical activity is a particular priority. The intervention has previously demonstrated efficacy with a volunteer population, and subsequently went through an iterative process of refinement in primary care, to maximise acceptability to both providers and recipients.

**Methods/ Design:**

This two arm cluster randomised controlled trial set in UK general practices will compare two strategies for increasing walking, assessed by pedometer, over six months. Patients attending practices randomised to the self-regulation intervention arm will receive an intervention consisting of behaviour change techniques designed to increase walking self-efficacy (confidence in ability to perform the behaviour), and to help people translate their "good" intentions into behaviour change by making plans. Patients attending practices randomised to the information provision arm will receive written materials promoting walking, and a short unstructured discussion about increasing their walking.

The trial will recruit 20 PN/HCAs (10 per arm), who will be trained by the research team to deliver the self-regulation intervention or information provision control intervention, to 400 patients registered at their practices (20 patients per PN/HCA). This will provide 85% power to detect a mean difference of five minutes/day walking between the self-regulation intervention group and the information provision control group. Secondary outcomes include health services costs, and intervention effects in sub-groups defined by age, ethnicity, gender, socio-economic status, and clinical condition. A mediation analysis will investigate the extent to which changes in constructs specified by the Theory of Planned Behaviour lead to changes in objectively assessed walking behaviour.

**Discussion:**

This trial addresses the current lack of evidence for interventions that are effective at increasing walking and that can be offered to patients in primary care. The intervention being evaluated has demonstrated efficacy, and has been through an extensive process of adaptation to ensure acceptability to both provider and recipient, thus optimising fidelity of intervention delivery and treatment receipt. It therefore provides a strong test of the hypothesis that a self-regulation intervention can help primary care patients increase their walking.

**Trial registration:**

Current Controlled Trials ISRCTN95932902

## Background

The Department of Health for England currently recommends that individuals should engage in at least 30 minutes of "moderate or vigorous" exercise, for at least five days each week, to gain health protective benefits [1]. Over 60% of men and 70% of women in England and Wales do not report meeting these requirements, and the proportion who actually meet them is likely to be considerably lower [2]. The Chief Medical Officer for England has recognised that many people have difficulty in translating a physical activity recommendation into daily life [3].

Brisk walking (i.e. walking of sufficient intensity to result in the walker getting slightly out of breath) is a form of moderate physical activity which is especially promising for health promotion because of its acceptability and accessibility, particularly among populations who are the most physically inactive [4]. It does not have to be scheduled, nor does it require any special clothes or equipment, so it is relatively low cost. Further, walking is low impact so minimises the risk of injuries and does not cause as much anxiety regarding adverse effects in sedentary populations as more vigorous forms of physical activity. There is meta-analytic evidence that increases in walking in previously sedentary adults increase fitness, and decrease body weight, BMI, percentage body fat and resting diastolic blood pressure [5]. That is, not only is walking acceptable to sedentary people, but it affords them considerable health benefits.

A recent systematic review and meta-analysis of 19 randomised and 29 non-randomised controlled studies provided evidence of the potential efficacy of walking interventions [6]. It concluded that "the most successful interventions could increase walking among targeted participants by up to 30-60 minutes a week on average, at least in the short term" [6]. The usefulness of this review was limited by including a mix of different types of interventions targeted at different populations, using different modes of delivery and different assessments of change in walking, which makes it difficult to identify the most effective intervention strategies. In addition the extent to which these interventions were sustainable, generalisable, or cost-effective is unclear, making interpretation to inform policy difficult.

A 2006 review from the National Institute of Health and Clinical Excellence (NICE) concluded that, although there is considerable evidence for the benefits that accrue from walking, there is a shortage of effective interventions that can be offered to patients in primary care [7]. This conclusion was unchanged when the review was updated in 2011. The advantages of a primary care setting are that this is where most of the population has regular contact with the healthcare system, and often in circumstances where they are receptive to advice to alter their behaviour. There has also been increased delivery of lifestyle advice by practice nurses (PNs) and healthcare assistants (HCAs), based in, or working closely with primary care. If an intervention to increase walking in primary care is effective and cost-effective, then primary care offers the possibilities of scaling this up to allow a large proportion of the population to receive the benefits of being more physically active.

The present study protocol describes a cluster randomised controlled trial of an intervention to increase walking in primary care which was designed to address the lack of effective interventions that can be offered to patients identified by NICE. In line with the Medical Research Council (MRC) framework for development and evaluation of complex interventions [8,9], the trial intervention and procedures build on previous formative research [10-14], based on explicit theory [15-17].

Extended developmental work was conducted using the Theory of Planned Behaviour (TPB), a social cognition model which can be used to predict and explain any behaviour in terms of a limited set of constructs [15]. A review of previous research using this theory identified perceived behavioural control (PBC) as the strongest predictor of intentions to walk more [13]. According to the TPB, PBC is underpinned by control beliefs: beliefs about which factors make it easy or difficult to perform the behaviour [15]. The most common control beliefs regarding walking in a general public sample [10] were identified as related to lack of time, indicating that the intervention should aim to address these beliefs. As PBC is a highly similar, if not identical, construct to self-efficacy [18], the literature on altering self-efficacy was consulted [16], which suggested that mastery experience was likely to be effective [16].

It is now well recognised that there is often a "gap" between intentions and behaviour [19]. Consequently, this intervention included not only a motivational component, to increase the intention to walk more, but also a volitional arm to enact those intentions [20]. This may be particularly important for walking, as the association between intentions and behaviour has been found to be low in past research [11]. This may be due to people reporting walking as being a means to achieve other goals, rather than a goal in itself, which is the case with many other forms of physical activity [12].

The formative research led to the development of a single session intervention of 15 minutes duration. It consists of techniques to increase self-efficacy (confidence in ability to perform the behaviour), and planning techniques to help people translate their "good intentions" into behaviour change [14]. This was done by, e.g. asking participants to recall previous walking successes [16] and by forming action plans about when, where, how and with whom they would increase their walking [17,20].

An evaluation of this intervention with 130 adult volunteers showed that it yielded large increases (Cohen's d = 0.90) in objectively assessed walking behaviour [14]. The mean increase of 87 minutes/week compares favourably with the mean increase of 30-60 minutes/week among the "most successful interventions" to promote walking identified by Ogilvie and colleagues [6]. These increases in objectively assessed behaviour were mediated by changes in walking self-efficacy, in line with the theoretical basis of the intervention, and were maintained for at least six weeks post-intervention. Further, similarly large effects on objectively assessed walking behaviour (d = 1.06) were obtained when the intervention was delivered to another volunteer sample by a person who was not involved in its development, indicating that the observed effects were due to the intervention itself, rather than the person delivering it [21]. The mechanism by which the intervention worked appeared again to be due to increasing self-efficacy, with little apparent effect of the intervention on self-reported planning [21].

The intervention was further developed following a subsequent meta-analysis that examined which intervention techniques [22] were associated with improvements in self-efficacy for increasing physical activity [23]. The technique of providing structured feedback was identified in the review as being associated with improvements in self-efficacy [23]. It was not included in the original intervention but has since been added to enhance the intervention's effectiveness. In addition, the technique of coping planning [17], which includes identification of barriers to physical activity, was removed, given that barrier identification was associated with poorer self-efficacy in the review. It was notable that those techniques which were associated with increases in self-efficacy were the same techniques which were associated with increases in physical activity (r = 0.69), providing further support for the idea that self-efficacy is a key determinant of such interventions [24].

The walking intervention has subsequently been extensively refined for delivery in primary care. A key aim of this refinement was to ensure provider fidelity of delivery to the intervention manual, and maximise recipient fidelity of receipt and enactment of the intervention techniques. If interventions are not delivered or received as intended (i.e. as per protocol) then it is difficult, if not impossible to be certain that the results can be attributed to the intervention itself [25]. This developmental work therefore tried to retain those key principles and elements of an intervention which had already demonstrated efficacy when delivered outside of a healthcare system to adult volunteers, and also optimise acceptability to both recipients and providers. Three phases of development work were conducted, before the current trial.

First, the intervention was revised, in an iterative fashion. A Research Nurse who was part of the research team delivered the intervention, based on an explicit manual, to patients in a single primary care practice within a local healthcare organisation, Coventry Primary Care Trust (PCT). Each intervention session was recorded, along with a brief interview with the intervention recipient conducted by a different research team member at the end of the intervention. On the basis of problems arising, the intervention was revised following discussion by the research team. The intervention was then further delivered, and revised, until it had been delivered to 10 patients, to optimise acceptability of the intervention to the patient recipients.

Secondly, two PNs and one HCA were trained, each delivering the intervention to four patients in their practices. The PN/HCAs were also interviewed prior to, and after, both the training and delivery to assess acceptability of the training and intervention materials. A sample of patients was also interviewed to establish comprehension and acceptability of the intervention. The training and intervention materials were then revised to optimise acceptability to PNs/ HCAs delivering the intervention.

Thirdly, an exploratory (pilot) trial was conducted, with 10 PNs/ HCAs recruited and trained, and eight delivering the intervention to up to 15 patients per practice. Two PNs were recruited and trained to deliver the control intervention to up to 15 patients per practice. In total, 66 intervention patients and 20 control patients participated. Data from three sources were collected during this pilot trial to assess treatment fidelity in relation to delivery and receipt of the intervention and to investigate reasons for variation in fidelity. Taped intervention sessions are being analysed to quantify the extent to which each intervention technique was delivered as specified by the intervention manual. Eight PN/HCAs were interviewed after they completed delivery of the intervention to investigate their experiences of delivering the intervention. Twelve patients were interviewed immediately after receiving the intervention, and three months later, to investigate patients' experiences of participating in the intervention, and specifically how the intervention was received.

The main outcome of this developmental work in primary care was that the intervention was refined, so as to be acceptable to both recipients and providers. We believe this work has provided a solid foundation of intervention development, based on an intervention with demonstrated efficacy in increasing objectively assessed walking and extensive adaptation to fit the primary care context, whilst retaining its theoretical underpinning. The next stage of this research is to examine the extent to which this developmental work has resulted in an intervention which can demonstrate efficacy in changing the walking behaviour of patients, when delivered in general practices by Practice Nurses or Health Care Assistants (PN/HCAs). In addition, it is unclear to what extent any intervention effects are sustainable and cost-effective, making interpretation to inform policy difficult.

The overall aims of the present research therefore, are to conduct a fully powered, definitive explanatory trial to:

(a) Assess the efficacy of the intervention in changing objectively assessed walking behaviour, for up to six months post-intervention.

(b) Identify key intervention mechanisms.

(c) Estimate the difference in the cost of the resources used by patients in each arm of the trial, and the cost-effectiveness of the intervention.

## Methods/Design

### Study Design

This explanatory trial is a two-arm cluster randomised controlled trial, with clustering by GP practice. It will assess differences in objectively assessed walking between patients who receive a brief self-regulation intervention, compared with patients who are provided with information about the benefits of walking. PNs/ HCAs randomised to the intervention group will deliver a brief self-regulation intervention to eligible patients, targeting self-efficacy and planning. PNs/ HCAs randomised to the "information provision" control group will provide information to eligible patients using materials which are currently widely available.

The study protocol was approved by Birmingham East, North and Solihull Research Ethics Committee (REC Ref: 09/H1206/116).

### Sample size

A total of 400 patients will be recruited from 20 PNs/HCAs (10 in each trial arm), each delivering the walking intervention sessions to 20 patients. Assuming a standard deviation of walking of 15 minutes/day, as obtained in a previous study with adult volunteers [14] and an intraclass correlation coefficient of 0.010, equal to the median value found in a review of clustering effects in practices in primary care [26], this will provide 85% power to detect a mean difference of five minutes/day walking between the intervention group, and the control group.

The difference in walking between groups that this explanatory trial is powered to detect is smaller than that observed in a previous study with adult volunteers [14] (12.4 mins/day over the first week, Cohen's d = 0.90) due to participants being primary care patients rather than volunteers, there being lower anticipated fidelity of treatment delivery, and a longer duration of outcome follow up.

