Patients in practices allocated to the intervention condition receive a final follow-up intervention session, which may be by telephone or face-to-face, two weeks after their second face-to-face session. Despite this, the measurement procedures for patients in practices in both conditions are identical from t2 onwards.

At six weeks post intervention (i.e. six weeks after t2 for both groups), all patients are sent a questionnaire by post (t3) containing the brief TPB measure, and a pedometer, and asked to return these by post. At six months post intervention (t4), all patients are sent a questionnaire containing a full TPB measure, the EQ5D, and a final pedometer, which again they are asked to return by post.

To encourage retention, all participants who complete and return questionnaires or pedometers from t2 onwards will be sent postal feedback on their walking behaviour and psychological measurements in the form of a postal profile. Those who do not send back the pedometer at any measurement point will receive a reminder letter and follow-up telephone calls from the research team encouraging them to return these, as loss of numerous pedometers will be expensive, and threaten the validity of the study.

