### Analysis

Planned intention-to-treat comparisons of the two groups at one week, six weeks and six months post-intervention (i.e. six months after t2 for both groups) will be conducted, with the primary dependent variable being mean daily walking, as assessed by pedometer. Mixed effects linear models will be fitted to compare the groups with a random practice effect to allow for clustering. The models will adjust for baseline characteristics at both practice and individual level. The former will include practice size and deprivation index, and the latter will include age, gender, BMI, ethnicity, employment status, educational level and clinical condition leading to referral.

As indicated above, the primary response will be the mean daily walking distance observed over up to seven days. Where less than five minutes walking is recorded for any particular day, the reading for that day will be treated as missing, and not used in calculating mean daily duration of walking. When individual days' data are missing, so long as data are available for two or more days, the mean will be taken over these non-missing days. If no data, or data from fewer than two days, are available for a particular patient at a particular timepoint, that assessment of walking will be treated as missing. These missing values will be imputed based on the baseline characteristics of the practice and individual [34]. A secondary analyses will be conducted excluding patients with missing data.

Planned exploratory sub-group analyses will be conducted to determine if the intervention has larger or smaller effects for groups defined in terms of age, ethnicity, gender, socio-economic status, or clinical condition, to provide information on any adverse impacts on social inequality.

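### The 85% power is calculated on all 400 recruited patients with no allowance for missing outcomes, so it holds only with near-complete pedometer data

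*Protocol article*

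**What the plan says.** The Sample size section of the protocol article sets the numbers: "A total of 400 patients will be recruited from 20 PNs/HCAs (10 in each trial arm), each delivering the walking intervention sessions to 20 patients". It continues: "Assuming a standard deviation of walking of 15 minutes/day, as obtained in a previous study with adult volunteers", with "an intraclass correlation coefficient of 0.010, equal to the median value found in a review of clustering effects in practices in primary care". From these it concludes that "this will provide 85% power to detect a mean difference of five minutes/day walking between the intervention group, and the control group". The abstract (Methods/Design) carries the same claim: "This will provide 85% power to detect a mean difference of five minutes/day walking". Neither place gives a loss rate or an inflation of the sample for loss.

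The Patient recruitment section aims for 20 participants per practice: further mail-outs follow only where the first 200 letters do not produce 20.

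Other sections foresee missing outcomes. Under patient consent, intervention and follow-up measurements, pedometers are returned by post after the intervention, at six weeks and at six months, and "Those who do not send back the pedometer at any measurement point will receive a reminder letter", followed by telephone calls. The Analysis section covers readings that do not arrive or are too sparse: "If no data, or data from fewer than two days, are available for a particular patient at a particular timepoint", the assessment counts as missing and is imputed from baseline characteristics of the practice and the individual.

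**The concern.** Power depends on the number of patients who contribute an outcome, not on the number recruited. Here the two are treated as equal, in a trial whose outcome depends on patients wearing a device at home and posting it back, the last time six months after the intervention.

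Imputation does not close the gap. A value predicted from baseline characteristics adds no outcome information beyond what the observed patients already supply, and the main model adjusts for the same kinds of characteristics.

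The Background describes the trial as fully powered and definitive. If it finds no difference, readers will judge that result against 85% power for five minutes/day. They should be able to see that this figure applies only when almost nobody is lost.

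**Working it through.** **Inputs from the Sample size section.** Difference 5 minutes/day; SD 15 minutes/day; ICC 0.010; 10 providers per arm; m = 20 patients each.

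**Assumptions of this check.** Two-sided 5% test (no significance level is given); one provider per practice, so 20 clusters; loss spread evenly over the clusters.

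**Formulas.**
- Design effect: DE = 1 + (m − 1) × 0.010
- Effective number per arm: n = 10m / DE
- Standard error of the difference: SE = 15 × √(2/n)
- Power (normal) = Φ(5/SE − 1.960)
- Difference detectable with 85% power (normal) = (1.960 + 1.036) × SE

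**Step 1: reproduce the stated figure.** With m = 20, DE = 1.19, n = 200/1.19 = 168.1, and SE = 15 × √(2/168.1) = 1.636. Then 5/1.636 = 3.056, and Φ(3.056 − 1.960) = 86.3%. This is close to the stated 85%, and it uses every recruited patient.

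**Step 2: how much margin there is.** Without clustering, 85% power needs 162 per arm. Multiplied by 1.19 and by 2 arms, that is 385.6, or 386 analysed patients. The margin is 400 − 386 = 14 patients with the design effect held at 1.19. Letting the design effect shrink with the cluster size, 19 per practice (5% loss) gives 84.9%.

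**Step 3: power at assumed loss rates.** The last column is a sensitivity figure. It uses the non-central t distribution with 20 − 2 = 18 practice-level degrees of freedom.

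| Loss (assumed) | m | DE | n per arm | SE | Power, normal | Detectable at 85% (min/day) | Power, t on 18 df |
|---|---|---|---|---|---|---|---|
| 0% | 20 | 1.19 | 168.1 | 1.636 | 86.3% | 4.90 | 82.4% |
| 5% | 19 | 1.18 | 161.0 | 1.672 | 84.9% | 5.01 | 80.7% |
| 10% | 18 | 1.17 | 153.8 | 1.710 | 83.2% | 5.12 | 79.0% |
| 20% | 16 | 1.15 | 139.1 | 1.798 | 79.4% | 5.39 | 74.8% |
| 30% | 14 | 1.13 | 123.9 | 1.906 | 74.7% | 5.71 | 69.9% |

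Example for 20% loss: DE = 1 + 15 × 0.010 = 1.15; n = 160/1.15 = 139.1; SE = 15 × √(2/139.1) = 1.798; 5/1.798 = 2.780; Φ(2.780 − 1.960) = 79.4%.

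**The case against.** The strongest reply is that the arithmetic is right: the stated inputs do give about 85%. Reminder and missing-data rules are contingency plans rather than a forecast of loss. Some provisions should limit loss: reminder letters, telephone calls, postal feedback to those who return data, and a threshold of only two usable days. Covariate adjustment may also recover precision. At 20% loss, 85% power needs an SE of 5/2.996 = 1.669. Since (1.669/1.798)² is about 0.86, covariates explaining about 14% of the variance would be enough.

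Most of this stands as a limit on the point. There is no calculation error, and the article predicts no particular loss. The possible gain from covariates is real, but the article claims none and gives no figure for it, so it cannot support an unqualified 85%.

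Stronger readings are tempting and should not be drawn:

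- **That power is really 70–80%.** No loss rate is given. By the normal approximation, which reproduces the stated figure, 80% corresponds to about 18–19% loss and 70% to about 38%. The lower end arrives sooner, at about 30% loss, only by also switching to a t reference.
- **That every one of the 400 must be analysed.** About 5% can be lost with power still at about 85%.
- **That 18 degrees of freedom should have been used.** With 20 clusters this is a sensible caution, but the normal approximation is a common planning method. The article specifies a mixed model without fixing its degrees of freedom, a detail commonly left to a fuller document.
- **That the pilot predicts a shortfall.** It reports "In total, 66 intervention patients and 20 control patients participated", well below 15 per practice, but 15 was a ceiling. In the main trial, providers consent to deliver to 20 patients and mail-outs are repeated. Recruitment yield is also a different question from missing outcomes.

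**Conclusion.** The point holds as an undisclosed assumption behind a definite claim. The 85% is power for the recruited number, and the design delivers it only with near-complete outcome data, up to about 5% loss. Beyond that the erosion is gradual: a shortfall of about 2, 6 and 10 percentage points from the stated 85% at 10%, 20% and 30% loss (83.2%, 79.4% and 74.7%). In terms of effect size, the trial at 20% loss has 85% power for about 5.4 rather than 5 minutes/day.

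These figures rest on the article's SD and ICC, a two-sided 5% level, even loss across practices and no gain from covariates. The loss rates are assumptions for illustration. On the t reference with 18 degrees of freedom, power is already 82% with complete data, which is a reason for caution and not evidence of a mistake.

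**What to change.** In the Sample size section and in the abstract, say what the figure assumes. Then give power either at the number of patients the sponsor expects to analyse or as a range. For example: *The 85% power assumes near-complete outcome data on all 400 patients; if 10%, 20% or 30% of outcomes are missing, power is about 83%, 79% or 75%.* The practice-level figures (82% with complete data; 79%, 75% and 70% at those losses) can be added as a sensitivity statement. If the sponsor has an expected loss rate, that single figure with its source is better than the range.

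The cost is one sentence in two places and a less favourable number. Recruitment, design and analysis stay as they are.
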